#### Integration/follow-up

2.3.9.

Participants will complete their first integration session with their assigned study facilitators 48 h post-dosing, prior to being discharged. Participants randomized to placebo will be offered the opportunity to return for open-label psilocybin dosing (0.25 mg/kg) approximately 2 weeks later (see section 2.3.10.1). Participants randomized to psilocybin will go on to complete three more integration visits 1, 2, and 12 weeks post-dosing, for a total of four integration visits.

Over the course of these integration sessions, facilitators will attend to, encourage, and support participants in describing and processing their psilocybin experience in a detailed manner (50). These discussions are meant to be open-ended, non-directive, unstructured, and participant-led, with the goal of aiding participants in consolidating any emergent insights from the dosing session and beyond, so as to utilize these insights as potential guiding principles for managing and living with OCD moving forward. During these integration sessions, facilitators will encourage participants to reference any journal entries, drawings, or other modes of creative expression that they may have engaged in post-dosing, to aid in discussing their psilocybin experience. During these sessions, facilitators will also document any new or persisting drug effects or AEs, and provide appropriate interventions if needed.

#### Optional trial components

2.3.10.

##### Open-label phase

2.3.10.1.

Participants randomly assigned to the placebo condition will be eligible for continued study participation in the open-label phase, which will be scheduled approximately 2 weeks after unblinding. These participants will be re-screened after unblinding to ensure that they still meet eligibility criteria, and verbally probed to ensure that they still consent to participate in the open-label phase. The open-label phase of the study will follow nearly identical procedures to those for participants randomly assigned to the psilocybin condition in the randomized phase (i.e., preparatory, dosing, and integration/follow-up visits). The only exceptions are that neuroimaging will be optional during the open-label phase, and there will only be one instead of two preparatory sessions (hence fewer nights of stay on the inpatient unit), given the already substantial interaction with study facilitators. Participants will be re-assessed on all study measures based on the same schedule as in the randomized phase. Participants need not complete any portion of the open-label phase, including the several subsequent follow-up visits, for their participation in the study to be considered completed. Data will be collected from all participants during the open-label phase for descriptive purposes but will be included only in secondary analyses of psilocybin’s effects on OCD and related symptomatology.

##### Qualitative interview

2.3.10.2.

An interview will be conducted by an independent interviewer one-month post-psilocybin dosing with all participants. This is optional, and participants will need to provide additional consent. This interview seeks to gather qualitative data about participants’ psilocybin experiences, insights, and any changes in OCD symptoms, quality of life, and functioning 1 month post-dosing.

### Outcomes

2.4.

#### Clinical outcomes

2.4.1.

##### Primary outcomes

2.4.1.1.

The primary outcome measures are the acute version of the clinician-administered Y-BOCS (AY-BOCS) (52) and the self-report Visual Analog Scale (VAS) for OCD symptoms (53), both of which assess OCD symptom severity over the past 24 h. These will be administered by independent raters at baseline and 24 and 48 h post-dosing. The Y-BOCS will also be administered by the same raters at baseline and 1, 2, 4, 8, and 12 weeks post-dosing.

Safety outcomes are included as primary outcomes as well. Safety measures assessed only during dosing include vitals and SUDs, and those assessed throughout the study duration include the Since Last Visit version of the C-SSRS (54), AEs, and any required changes to psychiatric or non-psychiatric medication regimens. The Since Last Visit version of the C-SSRS (54) assesses suicidal ideation severity, ideation intensity, and suicidal behavior severity (including non-suicidal, self-injurious behaviors) since the last assessment interval (i.e., the last study visit). AEs are defined as any untoward physical, social, economic, or psychological occurrence affecting participants, including any abnormal laboratory finding, symptom, reaction, or disease. An AE does not necessarily have a causal relationship with study procedures, and are graded as mild, moderate, or severe in this study. Severity of an AE is considered distinct from its “seriousness.” An AE is considered serious (i.e., SAE) if it: (1) is life-threatening; (2) results in hospitalization, disability/incapacity, a congenital anomaly or birth defect, or death; (3) requires medical or surgical intervention to prevent aforementioned outcomes; or (4) adversely affects the risk/benefit ratio of the study. Therefore, a severe AE is not necessarily an SAE.

To evaluate feasibility and tolerability, the following metrics will be tracked and reported. Specifically, we will report the total number of participants screened, found to be eligible, enrolled, had their enrollment confirmed, and randomized. We will also report on the total number of participants who were found to be ineligible, who voluntarily withdrew from participation prior to randomization, and who were excluded from participation due to safety concerns. In order to evaluate the restrictiveness of our eligibility criteria, we will report the number of participants excluded on the basis of different sets of criteria. Additionally, we will report the follow-up rates (i.e., number of participants who completed follow-up divided by the number of enrolled participants) by treatment arm for all study visits up to 12 weeks post-dosing. Number and percentage withdrawal from the trial with reasons for withdrawal will be summarized at each follow-up and by treatment arm. We will also summarize the number and percentage of participants with missing data for primary and secondary outcomes as a whole and by treatment group and follow-up intervals up to 12 weeks post-dosing. We will employ descriptive statistics and, if possible, logistic regressions to compare baseline characteristics of completers vs. participants with missing data at each follow-up interval.

##### Secondary outcome

2.4.1.2.

The secondary outcome in this study is resting-state brain connectivity, which will be assessed at baseline and 48 h post-dosing.

##### Exploratory outcomes

2.4.1.3.

Exploratory outcomes are assessed by clinician-rated or self-report measures that will be administered at baseline, immediately after dosing, and/or at varying follow-up intervals up to 12 weeks post-dosing. These measures include:

Obsessive–Compulsive Inventory-Revised (OCI-R) (55)Obsessive–Compulsive Trait Core Dimensions Questionnaire (OC-TCDQ) (56)Padua Inventory (PI) (57)State–Trait Anxiety Inventory (STAI) (58)Montgomery-Åsberg Depression Scale (MADRS) (59)Beck Depression Inventory, Second Edition (BDI-II) (60)Alcohol Use Disorders Identification Test (AUDIT) (61, 62)Drug Use Disorders Identification Test (DUDIT) (63)Self-Reported Nicotine Use (SRNU) (64)Obsessive Beliefs Questionnaire-44 (OBQ-44) (65)Thought-Action Fusion Scale (TAFS) (66)Responsibility Attitude Scale (RAS) (67)Big Five Aspects Scale (BFAS) (68)Quality of Life Enjoyment & Satisfaction Questionnaire-Short Form (Q-LESQ-SF) (69)Clinical Global Impression (CGI) – Clinician-Administered and Self-Report (70, 71)Sheehan Disability Scale (SDS) (72)Positive and Negative Affect Schedule-Expanded Form (PANAS-X) (73)Mystical Experience Questionnaire (MEQ) (74)Challenging Experience Questionnaire (CEQ) (75)5-Dimensional Altered States of Consciousness Rating Scale (5D-ASC) (76)Persisting Effects Questionnaire (PEQ) (77)Nature Relatedness Scale (NRS) (78)Pro-Environmental Behavior Scale (PEBS) (79)Individual Differences in Anthropomorphism Questionnaire (IDAQ) (80)Mind–Body Dualism Scale (MBDS) (81)Inclusion of Other in the Self Scale (IOS) (82)Ethics Position Questionnaire (EPQ) (83)Revised Life Orientation Test (LOT-R) (84)Schedule for Meaning in Life Evaluation (SMiLE) (85)Behavior Identification Form (BIF) (86)Pittsburgh Sleep Quality Index (PSQI) (87)Reactions to Research Participation Questionnaire (RRPQ) (88, 89)University of Rhode Island Change Assessment (URICA) (90)Utilization of Facility and Emergent Care (UFEC) (91)

Facilitators will administer paper self-reports of acute drug effects immediately post-dosing. The rest of the self-reports will be administered by research assistants *via* a link to the electronic data capture system on a tablet.

#### Evaluation of success of blinding

2.4.2.

Immediately prior to unblinding of participants at 48 h post-dosing, participants will be verbally probed to name the study arm they believe they were assigned to, with this response documented on the visit note.

### Facilitator competencies

2.5.

A separate manual (50) describes expected core competencies, skills, and theoretical orientation of study facilitators, as well as guiding principles for psilocybin dosing session facilitation. Because there is no structured program of psychological support tested in this trial, treatment fidelity is not assessed. Instead, study facilitators are expected to verify that they have thoroughly reviewed and understood the contents of the facilitation manual, and to continuously process and discuss their interactions with participants in study team meetings, to ensure that they are facilitating sessions according to guidelines in the manual.

### End of trial

2.6.

End of trial is defined as the time point at which the database is locked from data entry, which may be the same as or longer than the last time point of data collection (i.e., at the last follow-up visit with the final completer).

### Trial monitoring

2.7.

The PI will form a Data and Safety Monitoring Board (DSMB) comprising: (1) a psychiatrist with extensive OCD experience; (2) a cardiologist or internal medicine specialist; and (3) a general physician. The PI and DSMB will be responsible for safety oversight by monitoring the data, assuring protocol compliance, and conducting safety reviews every 6 months, including when reapproval of the protocol is sought. During the review process, the PI in collaboration with the DSMB will evaluate whether the study should continue unchanged, require modification or amendment, or close to enrollment; the latter two decisions will be communicated as soon as possible to the IRB/Human Investigations Committee (HIC). Either the PI, DSMB, or the IRB/HIC will have the authority to stop or suspend the study, or require modifications.

Additionally, the PI will periodically review the collection, storage, and distribution practices associated with the clinical data bank, and determine whether changes to enhance confidentiality and privacy are required. In terms of clinical monitoring, the research team will follow the Yale HIC’s guidelines for attribution and grading the severity of AEs, including determining whether an AE meets criteria for an SAE, and necessary follow-up IND reporting.

If the trial is prematurely stopped and terminated, the PI will be required to promptly inform active study participants, and provide appropriate therapy referrals if necessary and follow-up. All procedures and requirements pertaining to retention and storage of documents will still be observed. All other study materials will be treated in accordance with federal and state regulations.

### Data collection, storage, and security

2.8.

This study will be conducted within organizations fully bound by and compliant with HIPAA policies and strict research requirements. Data will be recorded in both written and/or electronic formats. Paper source documents/charts will be stored in locked filing cabinets in a locked office, while electronic records and data will be stored as password-protected files in secured computer(s) or server(s), all with access restricted to the PI and relevant study team members with appropriate training. Personal identifiers and protected health information (PHI) will be restricted to name, address, email address, phone number, birth date, and dates of study visits. PHI can be accessed only by the PI and specified research staff approved by the PI. No personally identifying data will appear in the digital data files or dissemination efforts (e.g., presentations, publications) resulting from this study. A Certificate of Confidentiality (CoC) has been obtained from the FDA for this study, providing additional protection for confidential participant data.

### Statistical analysis

2.9.

We will conduct linear mixed modeling (LMM) with restricted maximum likelihood estimation (to handle missing data) with appropriate alpha correction in SPSS to test our first hypothesis that psilocybin, compared to placebo, will improve OCD symptoms at the primary endpoint of 48 h post-dosing on the VAS for OCD symptoms and AY-BOCS. Treatment, time, and all interactions will be modeled as fixed effects. Participants will be modeled as a random effect. The time factor will be specified as baseline to 48 h post-dosing. Alpha-corrected *t*-tests will be used to probe interaction effects.

MRI preprocessing and group difference statistics will be evaluated using standard regression and general linear modeling approaches in a general-purpose MRI analysis package (QuNex), a processing platform that incorporates several state-of-the art neuroimaging tools (FSL, FreeSurfer, AFNI, SPM, PALM, and HCP-MPP) and thus offers comprehensive multimodal MRI analytic capabilities (92). To test the secondary hypothesis that at 48 h post-dosing, psilocybin, compared to placebo, will normalize frontostriatal connectivity at rest, we will conduct similar LMMs to examine the effect of psilocybin on activation of the corresponding regions. To test the secondary hypothesis that normalization of activity in these regions at 48 h post-dosing will correlate with clinical improvement in OCD symptoms (i.e., on the VAS for OCD symptoms, AY-BOCS, and Y-BOCS), we will conduct a correlational analysis with these variables.

Exploratory analyses of change in other secondary outcomes from baseline to 48 h post-dosing will be conducted using similar LMMs. Safety data will be presented as descriptive statistics. Data from the one-month post-dosing interviews will be qualitatively analyzed *via* interpretative phenomenological analysis (IPA) (93).

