### Trial design and setting

2.1.

This study (NCT03356483) will utilize a single-site, randomized (1:1), double-blind, active placebo-controlled, non-crossover design to examine the clinical and neural effects of either a single dose of oral psilocybin (0.25 mg/kg) or active placebo-control agent (250 mg of niacin) on OCD symptoms. Consistent with prior research (35, 45), unstructured, non-directive psychological support will be provided during the dosing session, as well as during two pre-dosing preparatory visits over the two consecutive days immediately before blinded dosing, and during four integration/follow-up visits (i.e., at 48 h, 1, 2, and 12 weeks post-dosing). The choice of unstructured, non-directive psychological support (as opposed to a more structured or manualized approach) is consistent with prior psilocybin clinical research. All preparatory and integration visits last for up to 2 h each.

This study will take place from November 2018 to June 2024 at the Yale OCD Research Clinic, housed within the Clinical Neuroscience Research Unit (CNRU) of the Connecticut Mental Health Center (CMHC) in New Haven, CT. The randomized phase of the study will be conducted as a 5-day inpatient stay on this locked, research-dedicated inpatient unit. The inpatient setting is logistically viable given the number of different study procedures to be completed per study day, as well as the medical and safety oversight afforded by an inpatient setting given the novel nature of the study. The choice of an inpatient setting was also strongly suggested by the Institutional Review Board (IRB) at the time of study development for ease of safety monitoring. While the study will be conducted on an inpatient unit, we do not require study participants to present with high acute risk; in fact, such participants are excluded from participation (see Section 2.3.2). Neuroimaging will be performed at the Yale Magnetic Resonance Research Center (MRRC), located in the Anlyan Center in New Haven, CT.

This study has undergone Yale Human Research Protection Program (HRPP) review and received IRB approval. This study has received Investigational New Drug (IND) approval (IND 134406) from the U.S. Food and Drug Administration (FDA) and is conducted under Drug Enforcement Administration (DEA) Schedule 1 research regulations.

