### Population of interest and sample size

2.2.

We will recruit adult participants aged 21 to 65 years old with a primary diagnosis of OCD and a Y-BOCS score of at least 19. A Y-BOCS score of 19 indicates moderate OCD symptom severity; with the criteria for a persisting diagnosis of OCD and the failure of at least one trial of standard care treatment (see Section 2.3.2), this cutoff score allows us to characterize our intended sample as treatment-refractory. Participants will be recruited irrespective of gender, sexual orientation, and ethnoracial identity. We used Optimal Design (46) to calculate sample size for a linear mixed-effects model with α = 0.05 (two-tailed), power = 0.80, and *d* = 1.5, which indicated that a total of 30 participants would be needed to detect a significant group effect at the primary endpoint per our first aim. The projected effect size of 1.5 appears reasonable given previously observed effect sizes for controlled trials of psilocybin in the treatment of major depressive disorder (45). Since this is the first study examining pre-post psilocybin resting functional connectivity changes in OCD with a placebo-controlled design, the functional connectivity analyses are largely exploratory in nature. A placebo-controlled study of psilocybin-induced connectivity changes at rest in predefined regions among 38 healthy controls detected several significant psilocybin-linked changes in mPFC connectivity (47), with Cohen’s *d*s ranging from 0.2 to 0.3. We speculate that psilocybin-linked connectivity changes may be even more dramatic in a clinical population. Assuming an attrition rate of 20%, we plan to enroll 36 participants to ensure 30 completers. Data collection is planned from November 2018 to October 2023.

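### The primary mixed model leaves baseline means free, so its 48 h test is an unadjusted change-score comparison; a baseline-adjusted 48 h contrast would usually be more precise at almost no cost

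*Protocol article*

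**What the plan says.** Section 2.9 (Statistical analysis) tests the first hypothesis, improvement at 48 h on the AY-BOCS and the VAS, with a linear mixed model fitted by REML: "Treatment, time, and all interactions will be modeled as fixed effects. Participants will be modeled as a random effect". It defines time in one sentence: "The time factor will be specified as baseline to 48 h post-dosing". Alpha-corrected t-tests then probe the interaction. The section mentions neither a baseline covariate nor baseline means held equal between arms.

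Section 2.4.1.1 (Primary outcomes) schedules both scales at three times: "These will be administered by independent raters at baseline and 24 and 48 h post-dosing". The Methods and analysis paragraph of the Abstract names only baseline and 48 h.

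Section 2.2 sizes the trial for a "linear mixed-effects model with α = 0.05 (two-tailed), power = 0.80" and an effect of d = 1.5, and concludes that "a total of 30 participants would be needed to detect a significant group effect at the primary endpoint per our first aim". It does not say whether d is in units of the endpoint SD or the change SD.

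**The concern.** Randomisation makes the two arms' baseline means equal in expectation. A model that estimates a separate baseline mean in each arm, and then subtracts it, spends information on a difference known to be zero on average. In a trial of 30 that can cost precision that the baseline ratings already collected could recover.

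Two points of wording add to this. The phrase that defines time fits two levels or three. With three, the interaction is no longer the 48 h comparison. Also, section 2.2 speaks of a group effect at the primary endpoint while section 2.9 works through an interaction, so the sample size is not tied in words to the test that will be reported. At stake are the width of the interval for the 48 h difference, power if the true effect is below 1.5, and an unambiguous primary test.

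**Working it through.** **Inputs from the article.** Two-sided alpha 0.05, power 0.80, d = 1.5, total N = 30 (section 2.2); 1:1 allocation (section 2.1), hence 15 per arm; fixed and random effects and the time factor (section 2.9).

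**Assumed.** The baseline-to-48 h correlation rho is not given, so a range is used. SDs are taken as equal unless stated, and d is in 48 h SD units.

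**1. The stated sample size.** A two-sample t-test at d = 1.5 needs 8.06, so 9 per arm (18 in total). With 15 per arm its power is 0.977. The figure of 30 is matched by a change-score test with rho = 0 (power 0.801). A treatment main effect averaged over two uncorrelated visits gives the same value. The article states neither assumption, so the match does not show what was done.

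**2. What the interaction is with two visits.** REML random-intercept fits to two simulated data sets of 30 gave the same t for the interaction as a t-test on change: -6.0196 by both routes, and -5.4572 by both routes.

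**3. Variance per unit sigma².**
- Change score (planned interaction): 2(1 - rho).
- Baseline-adjusted 48 h contrast: 1 - rho².
- Ratio: 2(1 - rho)/[(1 - rho)(1 + rho)] = 2/(1 + rho).

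The ratio is 1.67 at rho 0.2, 2/1.3 = 1.54 at 0.3, 2/1.5 = 1.33 at 0.5 and 1.18 at 0.7. The interval is wider by its square root: 1.24 times at rho 0.3 and 1.15 times at rho 0.5.

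**4. Power, 15 per arm, alpha 0.05.** For change, the noncentrality is d/√(2(1 - rho)) × √7.5 on 28 df. For the adjusted contrast it is d/√(1 - rho²) × √(7.5/(1 + 1/26)) on 27 df, where 1/26 allows for chance baseline imbalance. Example at d = 1.5, rho 0.3: 1.5/√1.4 × 2.739 = 3.47, power 0.918; and 1.5/√0.91 × 2.687 = 4.23, power 0.983.

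| d | rho | Change score | Baseline-adjusted |
|---|---|---|---|
| 1.5 | 0.2 | 0.880 | 0.977 |
| 1.5 | 0.3 | 0.918 | 0.983 |
| 1.5 | 0.5 | 0.977 | 0.994 |
| 1.06 | 0.3 | 0.66 | 0.82 |
| 1.06 | 0.5 | 0.80 | 0.89 |
| 1.0 | 0.3 | 0.608 | 0.775 |
| 1.0 | 0.5 | 0.753 | 0.849 |
| 1.0 | 0.7 | 0.927 | 0.952 |

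The value 1.06 is not in the article. It is the effect that a plain 48 h comparison detects with 80% power at 15 per arm.

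If the alpha correction for two outcomes means 0.025 each (an assumption), change-score power at d = 1.5 is 0.703 at rho 0, 0.805 at rho 0.2 and 0.858 at rho 0.3. The adjusted contrast gives 0.945, 0.953 and 0.963.

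**5. Unequal SDs (simulation, d = 1.06 in units of the placebo 48 h SD, alpha 0.05).**

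| Baseline SD | 48 h SD, placebo / psilocybin | rho | Change score | Baseline-adjusted |
|---|---|---|---|---|
| 0.7 | 1.0 / 1.0 | 0.3 | 77% | 82% |
| 0.7 | 1.0 / 1.0 | 0.5 | 88% | 89% |
| 0.7 | 1.0 / 1.3 | 0.3 | 67% | 70% |
| 0.7 | 1.0 / 1.3 | 0.5 | 79% | 78% |

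**6. If 24 h is included.** Treatment by three time levels has (2 - 1)(3 - 1) = 2 df, and the 48 h comparison becomes one of the follow-up t-tests. If the covariance were then a random intercept alone, all pairs of visits would be forced to one correlation. In simulation with no effect and equal SDs, correlations of 0.7 between the post-dose visits and 0.3 with baseline made the nominal 5% test of 48 h change reject about 8% of the time. Correlations of 0.8 (24 h with 48 h), 0.4 (baseline with 24 h) and 0.3 (baseline with 48 h) made it about 10%.

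**The case against.** The strongest reply is that the planned test is sound. With two time levels the interaction is one 1-df test. Section 2.9 ties the hypothesis to 48 h, and under randomisation the interaction has the same expected value as the 48 h group difference. Baseline as an outcome is no fault in itself, since a constrained-baseline model does the same. At d = 1.5 and alpha 0.05, power is at least 80% for every rho from 0 upward. All of this stands, and it limits the point to precision and wording.

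Equal SDs are also doubtful. Entry requires a Y-BOCS of at least 19, which may narrow the baseline spread of the related primary scales, and the gain then shrinks or slightly reverses (step 5). That stands too.

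A reader might infer more. One inference is that the plan has no single 48 h test and that post-hoc t-tests decide the result. The two-level reading contradicts this, and the article says only that the t-tests probe the interaction. Another is that the powered group effect is a treatment main effect averaged over baseline and 48 h, which would halve the effect and give 63% power at d = 1.5 and rho 0.5. But section 2.2 places the group effect at the primary endpoint, and section 2.9 proposes no decision on a main effect. A third is that the plan fixes a restrictive covariance. It names a participant random effect and leaves the residual structure unstated, which an article may leave to a fuller document. With two visits a random intercept restricts nothing that matters to the test.

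The reply does not settle whether time has two or three levels, and it does not explain why collected baseline data should go unused as an adjustment.

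**Conclusion.** The point holds as an inexpensive improvement in precision and clarity, not as an invalid or biased analysis. Under equal SDs the planned comparison carries 54% more variance than a baseline-adjusted one at rho 0.3 and 33% more at rho 0.5. At the design effect of 1.5 this moves power only from 92% to 98% (rho 0.3), with both above target. At an effect near 1.06 it moves power from 66% to 82% (rho 0.3) or from 80% to 89% (rho 0.5). These figures rest on 15 per arm, alpha 0.05 and assumed rho. With a baseline SD of 0.7 relative to 48 h, the difference runs from 5 points in favour of adjustment to 1 point against it.

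Separately, the article does not settle whether the 24 h rating enters the model. If it does, the interaction stops being the 48 h test. The group effect in section 2.2 and the interaction in section 2.9 share a target but should be worded as one contrast.

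**What to change.** - For each primary outcome, name one primary test: the treatment difference at 48 h, from a model with the baseline score as covariate or with baseline means constrained equal across arms. The constrained form stays within the mixed model already planned.
- State whether the 24 h rating is in the model. If it is, use treatment, visit and treatment-by-visit terms with an unstructured covariance, and take the 48 h contrast directly from that model without an interaction test as a gate.
- In section 2.2, describe the group effect as this 48 h contrast, and give the SD to which d = 1.5 refers and the assumed rho.

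The cost is a change of wording and one extra parameter; no new data or visits are needed. The downside is little or no gain, possibly a very small loss, if the baseline spread is narrow. The choice should be fixed and dated before any comparison of outcomes by arm.
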